### Randomisation method

2.5

A computer-generated block randomisation sequence will be created in advance via Microsoft Excel by the secondary investigator (SI), who is not involved in participant recruitment or eligibility screening. This approach ensures equal allocation (1:1) to the intervention and control groups, and the sequence will remain unchanged throughout the study (37).

Each eligible service user referred to the home care service will be assigned a unique sequential referral number for administrative tracking and eligibility screening. Following eligibility screening, written informed consent and baseline assessment, allocation will be performed by the SI via the concealed randomisation sequence stored in a password-protected file. This file is only accessible only to the SI to ensure allocation concealment until the moment of assignment.

### Participant blinding

2.6

The participants will not be informed whether they are receiving ICFIDCM or usual care (38, 39). Both groups will receive comparable regular professional contact and neutral communication to minimise the perception of group differences. The primary distinction between groups occurs through background care coordination mechanisms, with enhanced interprofessional collaboration and reasoning processes facilitated through the use of the ICF framework during case conferences in the intervention group vs. *ad hoc* coordination in the control group. Since participants are not directly involved in case conferences, group allocation differences will not apparently affect their service experience. As a result, participants remain unaware of whether they receive ICFIDCM or usual multidisciplinary care. In addition, while complete intervention provider (case manager, therapist and nurse) blinding is not feasible given the nature of the intervention, the research assistant responsible for collecting self-reported outcomes (WHODAS 2.0, SWLS) will remain blinded to group allocation to minimise bias.

### Procedures

2.7

All professional staff involved in the study underwent structured training in applying the ICF framework in interdisciplinary case management and using outcome measures before the trial began. This training, delivered by the Principal Investigator (PI), an experienced ICF educator and practitioner in rehabilitation, covered foundational and advanced topics. The training included the biopsychosocial model, ICF classification and coding systems, qualifiers, interdisciplinary case management and collaborative goal setting, interprofessional case conferences, practical application of the ICF Rehabilitation Set and Minimal Set of Environmental Factors, WHODAS 2.0, SWLS, and AusTOMs. Supervision meetings will be held quarterly to reinforce fidelity and ensure consistent application of the ICF framework across the interdisciplinary team.

The participants will be PWD who are newly referred and eligible service users of the HCS, YMMSS. Recruitment will be conducted by the HCS Team. Eligible PWD will be identified from the service user referral system. A supervisor from the Home Care Service will assign trained social workers, who will act as case managers, to approach potential participants and confirm their eligibility to be enrolled in this study. Once the participants are confirmed to be eligible, the case managers provide verbal and written information about the study, answer any questions, and obtain written informed consent from the participants.

Upon consent, baseline assessments, which will take place during the initial intake, will be scheduled. Participants will complete baseline questionnaires and assessments, including the WHODAS 2.0 and SWLS. To minimise bias, a research assistant who is not involved in intervention delivery and is blinded to group allocation will be responsible for distributing, assisting (if needed), and collecting these self-administered questionnaires from participants (40). This approach ensures that the data collection for these key self-reported outcomes remains unbiased, as the assistant does not know which group the participant has been assigned to (41, 42). Assessments of TROs, such as the AusTOMs and ICF qualifiers using the ICF Rehabilitation Set and Minimal Set of Environmental Factors, will be conducted by the professional team.

Following the baseline assessment, participants will be randomly assigned at a 1:1 ratio to either the intervention group or the control group, as stated before. This study is single-blinded: participants will not be informed of their group allocation, whereas the case managers and allied health professionals responsible for assessment and intervention delivery will be aware of the group assignments owing to the nature of the assessment/intervention.

The intervention group will receive structured ICFIDCM, which includes collaborative goal setting, monthly interdisciplinary case conferences, and coordinated care planning on the basis of ICF assessments. The control group will continue to receive usual multidisciplinary care involving standard discipline-specific assessments and interventions without structured interdisciplinary case management. During the six-month period, participants are permitted to continue all routine medical services and medications that participants are already receiving at baseline. The case managers will contact the case regularly via phone for check-in or service arrangements. If a participant is admitted to the hospital for new medical treatment or if their condition changes significantly, the case manager will notify the SI. Such events and any subsequent change in the intervention or usual care delivery will be recorded as protocol deviations.

All outcome assessments will be repeated at six months post-intervention. Throughout the study, participants' data and outcomes will be securely stored on an encrypted, password-protected server. Only authorised study personnel will have access, and data will be anonymised using the unique case referral number as the study code. Personal identifiers in documents are stored in locked filing cabinets to maintain confidentiality (Figure 1).

**Figure 1 F1:**
[figure not shown]
Flow diagram: study design and data collection procedures. ICFIDCM: International Classification of Functioning, Disability and Health-based interdisciplinary case management; WHODAS 2.0: World Health Organization Disability Assessment Schedule 2.0; SWLS: Satisfaction with Life Scale; ICF: International Classification of Functioning, Disability and Health; AusTOMs: Australian Therapy Outcome Measures.

### Intervention

2.8

Both intervention and control groups are served by the same interdisciplinary team of social workers, physiotherapists, occupational therapists, speech therapist, and nurses. Professional contacts will be individualised based on participants' clinical and functional needs, with frequency, duration, and intensity determined by routine service criteria. Since both groups are delivered in the same service setting and resource structure, protocol-driven differences in treatment intensity or overall service provision are not anticipated. All professional contacts will be systematically recorded. The primary distinction between groups lies in the care coordination structure, as detailed in Sections 2.8.1, 2.8.2.

#### Control group: usual multidisciplinary case management

2.8.1

The participants in the control group will receive conventional multidisciplinary rehabilitation services, where different professionals (e.g., social workers, physiotherapists, occupational therapists, speech therapist, and nurses) work independently in parallel with the limited integration of care plans. Rehabilitation goals are typically discipline-specific and reported during regular case conferences, whereas coordination among team members occurs on an as-needed basis (22).

#### Intervention group: ICFIDCM

2.8.2

The participants will receive an ICFIDCM programme, which involves collaborative assessment, interdisciplinary goal settings, and regular case conferences by an interdisciplinary team involving a social worker, physiotherapist, occupational therapist, nurse and speech therapist. To facilitate communication among different professionals, we adopt the conceptual framework of the ICF. This classification is based on two parts. Part one (functioning and disability) consists of 3 components: body functions and structures, activities, and participation. Part two (contextual factors) consists of 2 components: environmental and personal factors. The ICF provides a common language for describing the health states, outcomes and needs of clients, which improves communication between different professionals (24). In addition, it emphasises addressing not only functional impairments, but also environmental and personal factors that influence independence, participation, and overall well-being.

To apply the ICF framework more efficiently, specific core sets, the ICF Rehabilitation Set (also known as the Generic-30 Set) and the Minimal Set of Environmental Factors, with selected categories from the entire ICF category, are adopted to ensure that the relevant functions of people with disabilities are being addressed (26). For each of the selected categories, we will use ICF qualifiers to record the extent of the “problem” with respect to impairment, activity limitation and participation. ICF qualifiers are numeric measures coded after the relevant category code, which are essential to the meaningful use of the ICF classification (Table 1). For categories related to activities and participation domains, ICF qualifiers rate both performance, which describes what an individual does in their current environment, and capacity, which describes an individual's ability to execute a task or an action in a standardised environment.

**Table 1 T1:** Generic ICF qualifiers.

Code	Description
.0	No problem
.1	Mild problem
.2	Moderate problem
.3	Severe problem
.4	Complete problem
.8	Not specified
.9	Not applicable

For activities and participation, qualifiers are applied to both *Performance* and *Capacity*.

The environmental factors qualifiers indicate the extent to which an environmental factor acts as either a facilitator or a barrier. (Table 2).

**Table 2 T2:** ICF environmental factors qualifiers.

Code	Barrier (.)	Code	Facilitator (+)
.0	No barrier	+0	No facilitator
.1	Mild barrier	+1	Mild facilitator
.2	Moderate barrier	+2	Moderate facilitator
.3	Severe barrier	+3	Substantial facilitator
.4	Complete barrier	+4	Complete facilitator
.8	Barrier, not specified	+8	Facilitator, not specific
.9	Not applicable	+9	Not applicable

To gather information to rate the extent of impairment, limitations and restrictions, we will assess the health status of participants based on basis fo the different domains of the ICF (43, 44). These include body functions and structure through, e.g., BMI, pain, and mobility level; activities and participation through the Barthel index; modified functional ambulation classification; the Lawton Instrumental Activities of Daily Living Scale; and environmental and personal factors through, e.g., medications, the use of assistive devices, and family support.

During the initial assessment, similar to the usual care group, the participants (and their caregivers, if any) discuss their treatment goal(s) with the team. The goal-setting interview begins with the case manager, who is the social worker within the team, asking guiding questions on participants' life roles, challenges with daily routines and participation in the community, and then short- and long-term goals. The priorities and ways to integrate these goals into rehabilitation services are also discussed.

The first interdisciplinary case conference will be held after the initial assessment. The interdisciplinary team exchanges information, addressing the health status, identified functioning and contextual factors related to individual goals of rehabilitation. With the contribution of each professional staff member, common care goals addressing the needs of the individual to reintegrate into the community will be set, and an individualised care plan will be formulated. The goals of rehabilitation and related training contents, intensities, durations, completion criteria and responsible professionals will be set and discussed. The responsible case manager of each participant will oversee and integrate services across the interdisciplinary teams. Usually, the first case conference for each participant lasts for 45 min to 1 h. Afterwards, monthly case conferences will be held to review progress and adjust goals and interventions as needed, which usually take approximately 20–30 min per participant.

### Outcome measures

2.9

All participants will be assessed at baseline (preintervention) and after six months (postintervention) via the following assessment tools.

#### Primary outcomes

2.9.1

##### Assessment of functional and participation status

2.9.1.1

The 36-item self-administered version of the WHODAS 2.0 was used to assess functioning and participation across six domains: cognition, mobility, self-care, getting along, life activities, and participation. Participants rated their difficulty experienced in performing activities over the past 30 days on a 5-point Likert scale ranging from 1 (none) to 5 (extreme/cannot do). Domain and summary scores were transformed to a score range from 0 to 100, with higher scores indicating greater disability. Extensive research in 14 countries has shown the strong clinometric properties of the WHODAS 2.0, including internal consistency, reliability, validity, and responsiveness (45).

WHODAS was initially disseminated as WHODAS II, a 36-item instrument grounded in the ICF components of activity and participation, and was subsequently standardised in the 2010 WHO Manual as WHODAS 2.0, which superseded the earlier version while retaining the six-domain, 36-item structure (46). The present study adopted the validated Traditional Chinese self-administered version developed in Hong Kong (WHODAS II CT) (47). This version uses the same item content, response options, recall period, and scoring algorithm as the original 36-item schedule and is therefore equivalent in format and scoring to the WHODAS 2.0 36-item self-administered version described in the WHO manual. The Hong Kong validated study reported excellent internal consistency (Cronbach's *α* 0.89–0.98; overall *α* = 0.98), satisfactory construct validity (*χ*²/df = 3.05, Comparative fit index = 0.912), and good convergent validity in persons with disabilities and chronic illnesses, supporting its appropriateness for use in the present study.

##### Assessment of well-being by participants

2.9.1.2

The Chinese version of the SWLS (48) will be used to measure life satisfaction. This scale is a short five-item (e.g., “I am satisfied with my life”) scale based on a seven-point rating scale that ranges from 1 (strongly disagree) to 7 (strongly agree). The SWLS has demonstrated a good reliability coefficient of.82 (46) and has been employed in previous research using Chinese samples (*α* = .84) (49).

#### Secondary outcomes

2.9.2

##### Assessment of functional status by professionals

2.9.2.1

Score of ICF qualifiers: ICF qualifiers will be used to assess the baseline functional status of each selected category in the ICF Rehabilitation Set and Minimal Set of Environmental Factors. The score of each category is based on observed or self-reported data. The qualifier will be reassessed during postintervention assessment to record any changes in functional status (50). Previous studies have demonstrated the clinical utility, feasibility and inter-rater reliability of ICF qualifiers when applied with structured ICF core sets in rehabilitation settings (12, 13). The ICF Rehabilitation Set has shown acceptable content validity and feasibility in clinical validation studies, supporting its structured use for documenting functional status over time (26, 50).

##### Assessment of participation and well-being by professionals

2.9.1.2

AusTOMs: Developed by Unsworth & Duncombe (51), AusTOMs measure therapy outcomes for professionals, including occupational therapists, physiotherapists and speech pathologists. The scale, which is based on the WHO concept, contains 4 domains, which are impairment, activity limitation, participation restriction and distress. The Impairment domain describes structural (anatomical) or functional (physiological or psychological) difficulties that a client may have. The activity limitation domain measures a client's level of ability and difficulty in performing activities. The participation restriction domain examines, overall, the limitations that a client may experience in real-life, daily situations. The Distress/Wellbeing domain describes clients' and carers' level of concern. Concern may be evidenced by anger, frustration, apathy or depression. Abu-Awad et al. (51) confirmed the scale's concurrent validity and inter- and intrarater reliability.

## Data analysis

3

Data analysis will begin only after the follow-up stage. The PI and SI will have access to the final trial dataset. The quantitative data will be analysed via SPSS Statistics 27.0 (IBM). Data cleaning will include systematic screening for outliers and any inconsistencies in the data. Multiple imputations will be considered for missing data. Descriptive statistics will be applied as appropriate for all variables.

**Primary outcomes.** To determine whether functioning (WHODAS 2.0) and subjective well-being (SWLS) improve following the implementation of the ICFIDCM, we will compare intervention and control groups via generalised linear mixed models (GLMMs). Fixed effects will include time (baseline, 6 months), study group, and the group × time interaction, with participant ID as a random effect to account for repeated measures. The target test statistic will be the mean difference (with 95% confidence intervals), estimated via maximum likelihood methods. Two-sided significance will be set at 0.05. **Secondary outcomes.** To analyse the target secondary outcomes (ICF qualifiers and AusTOMs) over the course of time, descriptive analyses will first summarise change scores over time. Subsequently, GLMMs will be used to estimate group differences in changes, with the same fixed- and random-effects structure as above. The results will be expressed as estimated marginal means with 95% confidence intervals.

Treatment dosage variables (e.g., number of visits, total contact time) will be recorded and included as covariates in exploratory sensitivity analyses to assess their potential influence on treatment effects. Although the study is not powered for formal subgroup comparisons, exploratory sensitivity analyses will be performed to examine potential effect modification. Specifically, interaction terms between group allocation and age group, primary diagnosis, and treatment dosage will be examined within the mixed-effects model framework. These analyses are exploratory in nature and will be interpreted cautiously given the limited sample size.

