### Sample size determination

2.3

The primary outcomes of this study are PROs of functioning and well-being (WHODAS 2.0 and SWLS). We identified Hussain et al. (2025), who reported a between-group effect size of d = 0.8 on WHODAS 2.0 scores at the 20-week follow-up in a community-based, culturally adapted problem management intervention trial for people with disability (35). We use this study to inform our sample size calculation since the follow-up duration and outcome measure closely align with our six-month endpoint. Although Hussain et al. (2025) used the 12-item WHODAS 2.0 version, psychometric studies have demonstrated high concordance between the 12- and 36-item versions (correlation coefficients of *r* ≥ 0.915 between total scores on these two versions). This strong agreement supports the application of an effect size derived from the 12-item version to the 36-item WHODAS 2.0.

Using G*Power (G*Power 3, version 3.1.9.6) (36), with a α level of 0.05 (two-tailed), a power of 0.80, and an effect size of 0.8 as reported, a minimum sample size of approximately 26 participants per group (a total of 52 participants) was determined. Assuming a 15% attrition rate (18), the study will recruit a total of 60 participants who are PWD, newly referred and eligible service users of home care services. Considering that approximately 120–160 new case referrals are received per year, recruitment will take a minimum of 6 months.

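### The primary group × time model does not use the fact that baseline precedes randomisation, so it is less precise than a baseline-adjusted analysis and reaches the stated 80% power only if the baseline–follow-up correlation is about 0.49 or more

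*Protocol article*

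**What the plan says.** Section 3 (Data analysis, primary outcomes) analyses WHODAS 2.0 and SWLS with a mixed model: "Fixed effects will include time (baseline, 6 months), study group, and the group × time interaction, with participant ID as a random effect". The result is described as follows: "The target test statistic will be the mean difference (with 95% confidence intervals), estimated via maximum likelihood methods". No baseline covariate is listed, and nothing constrains the two arms to a common baseline mean. The secondary outcomes are given the same fixed and random effects.

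Section 2.7 (Procedures) fixes the order of events: "Following the baseline assessment, participants will be randomly assigned at a 1:1 ratio". Section 2.5 (Randomisation method) gives the same order.

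Section 2.3 (Sample size determination) relies on a cited trial that "reported a between-group effect size of d = 0.8 on WHODAS 2.0 scores at the 20-week follow-up". The calculation was run "with a α level of 0.05 (two-tailed), a power of 0.80, and an effect size of 0.8 as reported", and "a minimum sample size of approximately 26 participants per group (a total of 52 participants) was determined". Then: "Assuming a 15% attrition rate (18), the study will recruit a total of 60 participants who are PWD". No correlation between baseline and six months appears there or elsewhere in the article.

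**The concern.** Because baseline is measured before allocation, the true difference between the arms at baseline is zero by design. The group term in the model spends information on estimating that difference, and the interaction then subtracts the estimate in full. With 30 per arm, the chance baseline difference has a standard deviation of √(2/30) ≈ 0.26 SD units, and all of it enters the treatment estimate. A baseline-adjusted analysis removes only the share that the correlation supports.

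Two things are at stake. The first is precision, which is given up in a small trial although the baseline scores are being collected anyway. The second is the match between design and analysis. The sample size describes a comparison of one score per participant, whereas the planned test compares changes, and the power of that test depends on a correlation the article does not give.

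**Working it through.** **Inputs from the article.** Two-sided α 0.05, power 0.80, d = 0.8, 26 per group, 15% attrition, 60 recruited (Section 2.3); 1:1 allocation (Section 2.5); two visits (Section 2.9); model terms (Section 3).

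**Assumptions.** ρ is not given, so it is varied from 0.2 to 0.8. d is taken to be in units of the follow-up SD, the SDs are taken as equal at both visits, and the outcome is treated as continuous.

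**Step 1: reproduce the plan's figure.** A two-sample t test with n = 26 per group has noncentrality 0.8 × √(26/2) = 2.88 on 50 degrees of freedom. Power is 0.807; 25 per group gives 0.791. The stated 26 is reproduced, for a comparison that uses one score per participant. With 15% attrition, 60 × 0.85 = 51 are expected at six months.

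**Step 2: what the planned test is.** On a simulated complete data set with 26 per arm, the group × time coefficient and the plain difference in mean change agreed: both −0.9099, with standard error 0.2923.

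**Step 3: variances, in units of the follow-up variance.**
- Planned test (change): 2(1−ρ)
- Baseline-adjusted or common-baseline: 1−ρ²
- Ratio: 2(1−ρ)/(1−ρ²) = 2/(1+ρ)

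**Step 4: power at 26 per group.** The effective effect size is 0.8/√(2(1−ρ)) for the planned test and 0.8/√(1−ρ²) for the adjusted test, which also loses one degree of freedom. At ρ = 0.3 these are 0.8/√1.4 = 0.676 and 0.8/√0.91 = 0.839. Multiplying by √13 gives noncentralities of 2.44 and 3.02.

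| ρ | Variance ratio 2/(1+ρ) | Power, planned | Power, adjusted |
|---|---|---|---|
| 0.2 | 1.67 | 0.61 | 0.82 |
| 0.3 | 1.54 | 0.67 | 0.84 |
| 0.4 | 1.43 | 0.73 | 0.87 |
| 0.5 | 1.33 | 0.81 | 0.90 |
| 0.6 | 1.25 | 0.89 | 0.94 |
| 0.7 | 1.18 | 0.96 | 0.98 |
| 0.8 | 1.11 | 0.99 | 1.00 |

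**Step 5: where the planned test crosses 80%.** This is at ρ = 0.49 with 26 per group, 0.50 with 51 completers, and 0.41 if all 60 complete. For 80% power the planned test needs 41, 36, 31 and 26 per group at ρ = 0.2, 0.3, 0.4 and 0.5. The adjusted test needs 25, 24, 22 and 20.

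**Step 6: dropouts.** The likelihood model keeps participants who have baseline data only, so with attrition it is not exactly a change-score test. With 30 baselines and 25.5 follow-ups per arm at ρ = 0.4, the planned variance factor is 1.146 instead of 1.2. Power by normal approximation is 0.761, against 0.876 with a common baseline. The comparison is little altered.

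**The case against.** The planned model is a conventional choice and gives an unbiased estimate. Above ρ = 0.5 it does better than ignoring baseline altogether, and its power exceeds the stated 80%. By ρ = 0.7 the gap to the adjusted test is only about 0.02. All of this stands, and it confines the power shortfall to the lower part of the range of ρ.

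The article also does not say which standard deviation d = 0.8 was divided by. If it was the SD of change, the calculation of 26 per group would fit the planned test. That stands too: the follow-up-SD reading is natural for an effect reported at one follow-up time, but it is an assumption. The variance ratio does not depend on it.

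A reader might infer three stronger points that the article does not support:
- **That the trial is underpowered.** This would need a value of ρ, and none is given.
- **That the target could be the group main effect averaged over both visits**, since the mean difference is not tied to a coefficient. Section 2.1 states the hypothesis as greater improvement from baseline to six months, and Section 3 describes the secondary analysis, with the same model structure, as group differences in change. Both point to group × time.
- **That maximum likelihood makes the test invalid.** With about 52 participants and a t reference on 50 degrees of freedom, the type I error is about 5.4%. Larger figures require a normal reference, which the article does not state. This is minor.

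**Conclusion.** The point holds as one of efficiency and of match between analysis and sample size. The planned test carries 2/(1+ρ) times the variance of a baseline-adjusted test, which is 11% to 67% more over ρ = 0.8 to 0.2. This follows from the model terms and the order of baseline and allocation, given complete data and equal SDs at the two visits.

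The statement about 80% power is conditional. If d is also scaled to the follow-up SD, the planned test falls short only when ρ is under about 0.49, or about 0.41 if nobody is lost. At 26 per group the adjusted test meets 80% at every ρ, so adopting it removes the dependence on a correlation the article does not give. The plan does not produce a biased estimate, and no error in the figure of 26 per group is shown.

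**What to change.** In Section 3, name the between-group difference at six months as the target for each primary outcome, and estimate it in one of two ways:

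- a regression of the six-month score on arm with the baseline score as a covariate; or
- a constrained-baseline mixed model with time and one constructed indicator, equal to 1 only for intervention participants at six months, plus the random participant effect. The coefficient of that indicator is the treatment effect.

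Deleting the group term while keeping a categorical group × time factor does not impose the constraint. That design still has rank 4 and spans the same columns, so the fit is unchanged; the indicator has to be built explicitly. The constrained model also keeps participants with baseline data only, whom a complete-case covariate analysis would drop. This matters with 15% attrition expected.

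Apply the same structure to the secondary outcomes. Fitting by REML is an optional minor refinement.

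The cost is a few sentences in Section 3, one derived variable and changed model syntax, with no new data or participants. Section 3 says analysis starts only after follow-up, which Section 5.2 expects to be complete by 31 July 2026, so the change can be recorded before any outcome comparison is made.

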### Recruitment and consent procedures

2.4

Participants will be recruited from HCS operated by the Yang Memorial Methodist Social Service (YMMSS). New service users are identified through the service referral system. Trained social workers (case managers) approach potential participants, explain the study and obtain written informed consent at the participant's home. Written informed consent will be stored safely in the main office of the home care service teams.

Participants may withdraw from the study at any point without consequences. Dropouts will be recorded if a participant (a) withdraws consent or (b) dies before the follow-up assessment. Withdrawn cases will remain in the intention-to-treat analysis using their most recent available data. No dropout cases will be recruited.

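### The stated random-intercept model assumes equal spread at baseline and six months, so per-visit confidence intervals are mis-sized if the spread changes (minor)

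*Protocol article*

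**What the plan says.** All in the protocol article:

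- **Section 3, primary outcomes, mean structure.** "Fixed effects will include time (baseline, 6 months), study group, and the group × time interaction".
- **Section 3, primary outcomes, repeated measures.** The two visits are linked "with participant ID as a random effect to account for repeated measures". No second random term, residual covariance structure or robust standard error is named.
- **Section 3, primary outcomes, target.** "The target test statistic will be the mean difference (with 95% confidence intervals), estimated via maximum likelihood methods". The sentence does not say whether this is a difference in change or a difference at six months.
- **Section 3, secondary outcomes.** The models are fitted "with the same fixed- and random-effects structure as above" to estimate group differences in change. Then: "The results will be expressed as estimated marginal means with 95% confidence intervals".
- **Missing scores.** Section 2.3 plans the sample size "Assuming a 15% attrition rate". Section 2.4 counts withdrawal of consent and death as dropout and says: "Withdrawn cases will remain in the intention-to-treat analysis using their most recent available data". Section 3 adds: "Multiple imputations will be considered for missing data".

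No SD is given for any outcome at either visit, and nothing is said about whether the spread is expected to change.

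**The concern.** With two visits, a participant random intercept plus a single residual variance is a compound-symmetry model: one variance for both visits and one covariance between them. If six-month scores are more spread out than baseline scores, the model assigns each visit an average of the two variances. The six-month intervals then come out too narrow and the baseline intervals too wide. If scores contract, the reverse holds.

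This matters because the plan reports marginal means with intervals and does not stop at the interaction test. The primary target is also open to two readings. Section 2.1 frames the hypotheses as improvement from baseline, which points to a difference in change. Section 2.3 takes its effect size from a between-group difference at follow-up. If a six-month arm difference were what is reported, its interval would be mis-sized in the same way.

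There is a second, narrower route. Where a six-month score is missing and left to the model likelihood, the model uses the baseline score through a regression slope that is correct only if the two variances are equal.

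**Working it through.** **Inputs.** From the documents: two visits, 1:1 allocation, 60 recruited (30 per arm), 15% attrition, and the model above. Assumed, because the documents are silent: k = six-month SD / baseline SD, shown from 0.8 to 1.5, and a baseline to six-month correlation ρ = 0.6 where one is needed. Baseline SD is set to 1.

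**The plan's own figure.** The article gives none on this point. Its sample size (26 per group at d = 0.8, two-sided 0.05) reproduces: power is 79.1% at 25 per arm and 80.7% at 26. The covariance question does not touch it.

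**Step 1: per-visit intervals.** The pooled SD is √((1 + k²)/2). The six-month interval has width pooled SD/k relative to the correct one, and the baseline interval has width pooled SD/1. Large-sample coverage is 2Φ(1.96 × width ratio) − 1.

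Example, k = 1.25: the pooled SD is √((1 + 1.5625)/2) = √1.28125 = 1.132. The six-month ratio is 1.132/1.25 = 0.906, so coverage is 2Φ(1.775) − 1 = 92.4%. Baseline coverage is 2Φ(2.219) − 1 = 97.3%.

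| k | Six-month width ratio | Six-month coverage | Baseline coverage |
|---|---|---|---|
| 0.8 | 1.132 | 97.3% | 92.4% |
| 1.0 | 1.000 | 95.0% | 95.0% |
| 1.1 | 0.956 | 93.9% | 96.1% |
| 1.25 | 0.906 | 92.4% | 97.3% |
| 1.5 | 0.850 | 90.4% | 98.8% |

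A simulation with 30 per arm, complete data and 3,000 runs per setting agrees: six-month coverage is 97.1%, 94.8%, 92.8% and 90.8% at k = 0.8, 1.0, 1.25 and 1.5.

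**Step 2: six-month between-arm difference.** With complete data its model standard error is pooled SD × √(2/n), against a true k × √(2/n). The ratio is again pooled SD/k, so the six-month column above applies.

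**Step 3: group × time contrast, complete data.** The estimate is the difference between arms in mean change. The true variance of a change score is 1 + k² − 2ρk. The model's version is 2 × (1 + k²)/2 − 2ρk, which is the same quantity. The standard error is therefore right at every k. Simulated coverage is 95.0%, 95.7%, 95.1% and 94.9% at k = 0.8, 1.0, 1.25 and 1.5.

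**Step 4: missing six-month scores left to the likelihood.** The true slope on baseline is ρk. The model uses ρk/((1 + k²)/2). With ρ = 0.6:

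| k | True slope | Model slope |
|---|---|---|
| 0.8 | 0.480 | 0.585 |
| 1.0 | 0.600 | 0.600 |
| 1.25 | 0.750 | 0.585 |
| 1.5 | 0.900 | 0.554 |

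Effect on the group × time contrast with about 15% dropout depending on baseline (3,000 runs, Monte Carlo error of the bias 0.004 to 0.006 baseline SD):

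| k | Same pattern in both arms: bias, coverage | Opposite patterns by arm: bias, coverage |
|---|---|---|
| 0.8 | −0.004, 95.2% | 0.027, 94.3% |
| 1.0 | 0.003, 94.8% | −0.001, 94.8% |
| 1.25 | −0.001, 94.2% | −0.050, 93.9% |
| 1.5 | 0.003, 94.0% | −0.094, 93.7% |

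A smaller simulation of the opposite-pattern case (800 runs, about 16% dropout) gave −0.07 at k = 1.25 and −0.11 at k = 1.5. With an unstructured covariance the bias was at most 0.01.

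**The case against.** **The hypotheses are tested on the contrast, not on the per-visit means.** Section 2.1 asks about greater improvement, section 3 estimates group differences in change, and Step 3 shows that inference to be sound with complete data. This stands, and it is the main reason the point is small. It does not cover the marginal means that section 3 says will be reported, nor a primary mean difference whose time reference is not stated.

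**A reader might infer that dropout biases the primary result.** The documents do not support this. The bias needs four things together: changed spread, dropout related to baseline, that relation running in opposite directions by arm, and missing scores left to the likelihood. Section 2.4 instead carries forward the latest data for withdrawals and deaths, so no six-month value is left for the model to fill, and section 3 mentions multiple imputation as a possibility. Only scores missing for other reasons, and not imputed, would be exposed. Whether carry-forward is itself sound is a separate question.

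**A lone random intercept with one residual variance is an inference.** Section 3 does not describe the residual covariance, and an article may leave that to a fuller document. This is fair as a caution. Still, the article does name the participant effect as its device for repeated measures and reuses it for the secondary outcomes. The point therefore rests on what is stated.

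**The normal-theory calculation may not suit every outcome.** ICF qualifiers are 0 to 4 ratings per category (Table 1). The figures above apply only to outcomes analysed as continuous.

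**Conclusion.** The point holds in a limited form. As written, the model assumes equal variance at the two visits. If that fails, the per-visit marginal-mean intervals are mis-sized, and so is that of any six-month arm difference taken from the model. Six-month coverage falls by about 1 percentage point at an SD ratio of 1.1, 2.6 points at 1.25 and 4.6 points at 1.5. If spread contracts, the shortfall moves to baseline.

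It would go too far to say that the intervals are wrong. No SD is given, nothing in the documents predicts a change in spread, and at a ratio of 1.0 there is no error. The group × time contrast is valid with complete data. With similar dropout patterns in both arms its bias is about zero and its coverage 94.0% to 95.2%. A bias of up to about a tenth of a baseline SD appears only in the stress case and only for scores left to the likelihood.

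The sample size is unaffected. Severity is minor: a low-cost improvement in specification that the sponsor may choose to adopt.

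**What to change.** In section 3, for outcomes analysed as continuous, replace the participant random intercept with an unstructured 2 × 2 within-participant covariance by visit (visit as the repeated effect). Each visit then has its own variance, which sizes the per-visit intervals correctly and makes the slope for any score left to the likelihood equal to ρk.

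In the same section, state that the reported mean difference is the between-arm difference in change from baseline to six months, with its 95% CI, and give it beside the marginal means for the secondary outcomes.

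The cost is a change of wording and one extra covariance parameter, with negligible loss of efficiency if the variances are in fact equal. No new data are needed. Section 3 starts analysis only after follow-up, which section 5.2 expects to end by 31 July 2026, so the choice can be fixed before the data are analysed.
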